#### Group 1: Verbal information only (usual care)

2.6.1

Patients will receive their usual verbal information from the dentist following their check-up. The dentist will mark any of the six main areas of recommended actions covered in the conversation, on a printed credit-card sized card, which will then be given to patient to take away (Fig. 3). The advice ‘*Following your dental treatment plan*’ relates to returning for future dental visits which have been scheduled for that course of treatment.

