### Data collection procedures

2.12

Data will be collected at baseline, then 2–3 weeks later when the patient returns for their first treatment visit (second dental visit, V2), and then at 5–6 weeks post intervention (third dental visit, V3), (Fig. 6, Table 1). Since eligible patients are those at medium/high risk of poor oral health, we expect the patient to need to return for further care, and so we will collect data opportunistically at this time. At these V2 and V3 follow up visits, the dentist will measure BPE (before the patient receives usual care treatment), and a further QLF photograph will be taken (not shown to the patient) to enable a change in plaque coverage and demineralisation to be measured from QLF images. Participants will be asked about any change in behaviour in relation to the messages (Fig. 3) listed on the printed cards (given to all patients at the first visit), using the item stem ‘*Since my last appointment I have* …. ’.

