#### Analysis of clinical outcomes

2.13.3

Clinical outcomes will be analysed at the first short term follow-up visit, no more than three months post-randomisation. All QLF images will be rated as good/poor quality by the assessor (blinded to group allocation). Those not judged to be of sufficient quality to accurately generate the outcome variables will be excluded from the analysis. Analysis of the three QLF generated variables will use general linear models, with value of the variable of interest at the first short-term follow-up appointment as the outcome variable, and intervention group allocation as a fixed factor. Baseline value of the variable of interest will be included as a covariate. All analyses will follow the intention to treat principle as far as is practically possible.

Basic Periodontal examination (BPE) scores will be analysed by categorising each patient into one of four outcome categories. 1 – stable healthy (code 0 at baseline and follow-up), 2- stable bleeding (code 1 or greater at baseline and follow-up), 3 – change to bleeding (code 0 at baseline, code 1 or greater at follow-up), and 4 – change to healthy (code 1 or greater at baseline, code 0 at follow-up). The analysis will use multinomial logistic regression to test the effect of intervention group on outcome, with the primary hypothesis of interest between groups 2 and 4.

Multiple imputation analyses will be carried out to investigate the robustness of the results to missing data. Using all the data which is available, including baseline variables, five complete case data sets will be imputed, and each analysed in the same way. The results can then be combined, and compared with the analysis excluding missing data, to assess whether this would be likely to change the overall conclusions.

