## Discussion

3

Reform of the NHS dental contract is based on a reorientation from a treatment-focused service, to one which prioritises prevention of disease; with patients participating by improving their oral health behaviours to minimise the (re-)occurrence of disease. The idea follows a general drive towards emphasising that patients have a shared responsibility for maintaining their health. Over 75 NHS dental practices are currently testing two alternative prototypes in England; both using a categorisation of patients according to a Traffic Light scheme, with this information communicated to patients at their dental check-up. This study is therefore set to directly inform national policy, relating to whether patients value risk information in this form. A recent non-randomised study in six NHS dental practices which compared a new model involving a traffic light risk assessment of patients, with other practices using the previous model of dental practice care, found only 291 of 550 participants recruited attended both baseline and follow up appointments (53%). This suggests that long term follow up of patients in a study such as this may present challenges [50]; and recruitment of dental patients to a trial set in dental practice, especially those with a high/medium risk of oral disease, may present further challenges [51]. Nevertheless, when considered against the continuum of pragmatic as opposed to explanatory trials, this study is designed to be at the pragmatic end of the spectrum, since its purpose is to examine the intervention (communication of risk information) under the usual conditions in which they will be applied [52]. The trial will be supported by embedded qualitative work to support understanding the contextual issues influencing the implementation of the intervention, and the trial itself.

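### Five imputations are fixed without reference to how much is missing, and agreement with the complete-case analysis would not rule out outcome-dependent return to the practice

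*Protocol article*

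**What the plan says.** Section 2.13.3 (Analysis of clinical outcomes) specifies three things about missing data.

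- The number of imputations: "five complete case data sets will be imputed, and each analysed in the same way".
- The information used: "Using all the data which is available, including baseline variables".
- How the result is used. It is to be "compared with the analysis excluding missing data, to assess whether this would be likely to change the overall conclusions".

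The same section sets the time point: "Clinical outcomes will be analysed at the first short term follow-up visit, no more than three months post-randomisation". It also drops QLF images of poor quality, at a rate that is not given.

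Section 2.12 (Data collection procedures) explains how the follow-up values arise: "we expect the patient to need to return for further care, and so we will collect data opportunistically at this time". A patient who does not come back has no follow-up PPI, demineralisation, ΔQ or BPE value.

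Section 2.6.1 describes the advice card. One item is following the treatment plan, which "relates to returning for future dental visits which have been scheduled for that course of treatment". Sections 2.6.2 and 2.6.3 give the same card content to the other two arms.

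No attrition rate is forecast for the clinical outcomes. The only allowance in section 2.10 is about 20%, for refusal to answer the willingness-to-pay questions. The Discussion reports that in another, non-randomised study in dental practices 291 of 550 participants (53%) attended both appointments, and concludes: "This suggests that long term follow up of patients in a study such as this may present challenges".

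**The concern.** Two features of the stated check weaken it.

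First, five is fixed without reference to the missing fraction. Multiple imputation adds simulation noise that grows with the fraction of missing information and shrinks with the number of imputations. If much is missing, a gap between the imputed and complete-case results, or the lack of one, may be partly due to the random draw.

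Second, whether an outcome is observed depends on a behaviour that the advice targets. Section 2.2 says that risk messages can produce defensive responses and links imagery in particular with defensiveness, so return that differs by arm is plausible. Imputation from observed data in the ordinary way assumes missing at random; the article does not state this, and it is inferred from the method. If return depends on the unobserved outcome, and does so differently by arm, imputation and complete-case analysis can agree while both are biased. The plan would then read that agreement as robustness.

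**Working it through.** **The plan's own figures.** There is no stated figure for imputation precision. The related figures reproduce:

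- 291/550 = 52.9%, stated as 53%, so 47% did not attend both appointments.
- PPI, 133 per group, difference 3.5, SD 10: SE = 10 × √(2/133) = 1.226. 3.5/1.226 = 2.854, and 2.854 − 1.96 = 0.894. Power is 81%, stated as 80%.

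**Noise with five imputations.** Let FMI be the fraction of missing information and m the number of imputations. FMI is set equal to the missing share, which is an assumption. The 47% is borrowed from the cited study; 20% and 10% are assumed values to show the range.

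- Monte Carlo SD of the pooled estimate, in units of its SE: √(FMI/m)
- Relative efficiency: 1/(1 + FMI/m)
- Coefficient of variation (CV) of the SE: about FMI/√(2(m − 1))
- Rubin degrees of freedom: (m − 1)/FMI²

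| FMI | m | Monte Carlo SD / SE | Relative efficiency | CV of SE | df |
|---|---|---|---|---|---|
| 0.47 | 5 | √0.094 = 0.31 | 0.91 | 17% | 18 |
| 0.20 | 5 | √0.040 = 0.20 | 0.96 | 7% | 100 |
| 0.10 | 5 | √0.020 = 0.14 | 0.98 | 3.5% | 400 |
| 0.47 | 50 | √0.0094 = 0.10 | 0.99 | 5% | 222 |

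If m equals the percentage of incomplete cases, then m = 100 × FMI and the Monte Carlo SD is √(1/100) = 0.10 SE at any missing share. To hold the CV of the SE at 5%, the rule m = 1 + 0.5 × (FMI/0.05)² gives about 46 imputations at FMI 0.47, 19 at 0.30, 9 at 0.20 and 3 at 0.10.

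A simulation checked the worst row: 133 per arm, 47% missing, SD 10, baseline correlation 0.5 (assumed). Repeating the imputation with m = 5 on the same data moved the estimate by an SD of 0.44 PPI points and the SE by 18%. The 5th to 95th percentile range of the p-value averaged 0.20, against 0.03 with m = 50.

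**What agreement with complete cases can show.** A second simulation set the true effect to 0 and let the probability of return depend on the part of the outcome that baseline does not explain. The imputation model held arm and baseline only. Effects are in PPI points.

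| Return | Complete case | Imputation |
|---|---|---|
| Equal rates (53%), same moderate dependence in both arms | 0.04 | 0.02 |
| 48% against 59%, same moderate dependence | 0.50 | 0.49 |
| Equal rates, moderate dependence in one arm only | −1.96 | −1.97 |
| Equal rates, strong dependence in one arm only | −3.40 | −3.42 |

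The two analyses agree in every row, whether or not there is bias. In the last row the bias is about the size of the 3.5-point target.

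**Size of departure that matters.** If the missing values in one arm are shifted by delta, the effect moves by missing share × delta. To move it by 3.5 points takes 3.5/0.47 = 7.4 points (0.74 SD) at 47% missing, 3.5/0.20 = 17.5 points (1.75 SD) at 20%, and 3.5/0.10 = 35 points (3.5 SD) at 10%.

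**The case against.** The strongest reply has four parts.

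1. *The 47% is not this trial's figure.* A reader might infer that about half of the clinical outcomes will be missing. The documents do not support that. The figure comes from another study, and the Discussion uses it to warn about long-term follow-up. The clinical endpoint is the first return visit, usually 2–3 weeks after baseline, in patients expected to need further care. This stands: 47% is a scenario. At 20% the noise is modest and at 10% it is small.

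2. *The check is not blind.* A reader might infer that comparing imputation with complete cases can show nothing about return. That goes too far. The complete-case model for the QLF outcomes conditions on arm and the baseline value, whereas the imputation uses all available data. By Table 1 these include the EPPM items and the 6- and 12-month self-reports, which do not require a visit to the practice. Such data can capture part of the dependence and lower the fraction of missing information. Only what the observed variables leave unexplained escapes, and the second simulation, with baseline alone in the imputation model, describes that part.

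3. *Different return rates are not bias in themselves.* This also stands. Bias needs return to depend on the outcome, and that dependence or the return rate to differ by arm.

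4. *A detailed analysis plan is promised in section 2.13 and is not shown.* A seed, a table of return by arm or a missing-not-at-random analysis may be there, so their absence from the article is no fault. The number five and the use made of the comparison are, however, stated in the article.

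**Conclusion.** The point holds within limits. The article fixes five imputations for outcomes whose availability depends on return to the practice, and takes agreement with complete cases as its evidence of robustness. If attrition resembled the cited study, five would leave Monte Carlo noise of nearly a third of a standard error in the pooled estimate, and about three times less with 50. At low attrition five would do little harm, but nothing in the article shows that attrition will be low. Separately, and for any number of imputations, agreement would not exclude bias from return that depends on the unobserved outcome differently by arm.

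This rests on FMI equal to the missing share, on missing at random as the inferred imputation assumption, and on assumed return mechanisms in the simulation. It does not show that such bias will occur. The main clinical analyses use observed data and are not altered by the number of imputations. The primary willingness-to-pay values for all three forms are elicited before the information is given and do not depend on return.

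**What to change.** In section 2.13.3, or in the analysis plan as the governing text:

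- Replace five with a number at least equal to the percentage of incomplete cases, for example 50. This holds the Monte Carlo SD at about 0.10 SE or below under the assumption above.
- Unless the analysis plan already has it, add a delta-adjusted imputation for PPI and BPE. Shift the imputed values of non-returners away from the missing-at-random prediction, let the shift differ by arm, and extend it to the point where the conclusion changes. For BPE, apply the shift to the log odds of a healthy code at follow-up.
- State that agreement between imputation and complete cases will not on its own be read as robustness.

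The cost is minutes of computing and one sensitivity table. No new data are needed, and the main analyses do not change.

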### Ethical considerations

2.14

Liverpool Health Partners is the research sponsor (Approval reference no: UoL001042). Favourable ethical opinion for the study was confirmed by the North West, Liverpool-East National Research Ethics Committee on 1.8.14 (REC reference number 14/NW/1016). A subsequent substantial amendment in ethical approval was obtained on 18.3.16 to allow a prize draw of ten lots of £25 for patients completing follow up data collection at 6 and again at 12 months (£500 total). NHS Research Governance approval was obtained from The Royal Liverpool and Broadgreen University Hospitals NHS Trust on 20.8.14 (reference number 4819).

Participants meeting eligibility criteria will be given a Patient Information Sheet by dental practice staff which will provide all details of the study procedures, rights to withdrawal, anonymity, confidentiality, along with details of the research team; and have the opportunity to ask questions before informed consent is taken by a member of dental staff trained in GCP.

Participant details will be recorded on a recruitment log to facilitate follow-up data collection. Participants will be assured that all data will be anonymised and stored on a database under the guidelines of the 1998 Data Protection Act. No patient-identifiable information will be sent via electronic means (use of coded study number, patient's sex and patient's age only). Any patient identifiable information (e.g. recruitment logs), will be collected in person from dental practices by a member of the research team rather than electronically. Data and study documentation will be archived at the University of Liverpool for at least five years after the completion of the study in line with associated regulations.

## Discussion

3

Reform of the NHS dental contract is based on a reorientation from a treatment-focused service, to one which prioritises prevention of disease; with patients participating by improving their oral health behaviours to minimise the (re-)occurrence of disease. The idea follows a general drive towards emphasising that patients have a shared responsibility for maintaining their health. Over 75 NHS dental practices are currently testing two alternative prototypes in England; both using a categorisation of patients according to a Traffic Light scheme, with this information communicated to patients at their dental check-up. This study is therefore set to directly inform national policy, relating to whether patients value risk information in this form. A recent non-randomised study in six NHS dental practices which compared a new model involving a traffic light risk assessment of patients, with other practices using the previous model of dental practice care, found only 291 of 550 participants recruited attended both baseline and follow up appointments (53%). This suggests that long term follow up of patients in a study such as this may present challenges [50]; and recruitment of dental patients to a trial set in dental practice, especially those with a high/medium risk of oral disease, may present further challenges [51]. Nevertheless, when considered against the continuum of pragmatic as opposed to explanatory trials, this study is designed to be at the pragmatic end of the spectrum, since its purpose is to examine the intervention (communication of risk information) under the usual conditions in which they will be applied [52]. The trial will be supported by embedded qualitative work to support understanding the contextual issues influencing the implementation of the intervention, and the trial itself.

### Study status

3.1

The first patient was recruited in August 2015. Twelve-month follow up data collection will be completed by October 2017.

